### Premature Withdrawal of Patients from Study

Patients are free to withdraw consent and discontinue participation at any time without penalty and are not obliged to give a reason. Patients may be withdrawn/removed, if necessary, to protect their health or the integrity of the study. The Investigator also has the right to withdraw patients from the study in the event of intercurrent illness, adverse events, treatment failures, protocol violations, administrative, or other reasons. When a patient withdraws from the study, all safety data normally required at the completion of the study will be obtained, where possible. All details available will be reported and recorded for any patient that withdraws or is removed from the study.

If the reason for removal of a patient from the study is an adverse event, intercurrent illness, or an abnormal laboratory value, the principal specific event or test will also be recorded on the case report form (CRF).

CRFs are required for all patients who receive study medication, even if they subsequently withdraw from the study before all assessments are completed. All sections of the CRF, up to the time of withdrawal, are to be completed. Efforts should be made to obtain complete information regarding the tolerability and safety of the test drug. This means that asking for and recording Adverse Events should continue whenever possible. Patients who withdraw from the trial will not be replaced.

All patients who withdraw early from the study but have received all days of study medication will be included in the analysis of effectiveness.

All patients who withdraw from the study but receive at least one dose of study medication will be included in the analysis of safety.

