## Selection and Withdrawal of Patients

### Inclusion Criteria

1. Male or female, age 21-65 years
2. Fever of  38C (directly measured or patient reported) of  48 hr duration.
3. At least two of the following criteria indicating probable dengue infection:
   1. Live or work in or recent travel to dengue endemic area
   2. Nausea and vomiting
   3. Presence of rash
   4. Aches and pains, including headache, or retro-orbital, muscle or joint pain
4. Positive NS1 strip assay or PCR
5. Able and willing to give written or oral informed consent
6. Willing to be an inpatient for from Study Day 1 to 5, and to return to the IMU on Study Days 7, 10, and 15.
7. Willing to keep a diary of pain medication usage and side effects

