
Patients will be asked to return to the IMU on Study Days 7, 10, and 15 for blood draws, urinalysis, completion of a VASP, and safety assessments. Estimated total blood volume taken per patient is ~ 200 mL during Study Days 1 to 5 and ~ 80 mL for Study Days 7 to 15. The patient will complete the study on Study Day 15 after the investigator has completed the final assessment, unless ongoing adverse events require monitoring. Patients unable to complete the entire course of drug treatment will be asked to complete all planned in-patient and out-patient assessments.

The sponsor will cover all costs for drugs, procedures, consumables and hospitalization stay (Class A ward) related to dengue illness through Day 15 or effects related to celgosivir usage. Participants in the trial will receive compensation for participation in the study.

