## Criteria for Discontinuation of Patient Study Drug and for Study Termination

A patient’s study drug will be discontinued for

1) any patient developing severe dengue based on WHO criteria or

2) any patient developing grade 3 severity diarrhoea

The study will be terminated at any time that the Data Safety and Monitoring Board members conclude that:

1) Clear and significant harm is noticed in the treatment;

2) ≥30% serious adverse reactions occur in the treatment arm that are possibly, probably or definitely related to study drug;

3) ≥30% patients develop severe dengue based on WHO criteria;

4) ≥30% patients develop grade 3 severity diarrhoea;

5) The drop out rate is too high (>30%).

Figure 2 Flowchart of patients’ activities

Placebo

(N = 25)

Celgosivir

(N = 25)

Drug administration

Drug administration

Daily assessment

Daily assessment

Return to IMU for assessment

Return to IMU for assessment

Visit to polyclinic or GP/ED of NUH or SGH

Assessment of high probability of dengue infection

Fever ≥38° of ≤ 48 hr duration

≥2 symptoms of dengue fever

Positive NS1 strip assay

Others

Referral to IMU for screening of other inclusion & exclusion criteria

Written inform consent

Baseline assessment

Randomization

Discharge

End of Study

Day 5

Day 1

Day 1 to Day 5

Days 7, 10, 15

Day 15

Prior to Day 1

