## Statistical analysis

A detailed statistical analysis plan will be prepared prior to unblinding.

General

Continuous variables will be summarized using mean and standard deviation. Categorical variables will be summarized by frequency and percentage. Percentages will be rounded to one decimal place and, therefore, may not always add up to 100. All statistical tests will be set at a 5% level of significance. All confidence intervals will be 95% and two-sided. Statistical analyses will be performed using SAS version 9.3.

Demographic and baseline characteristics

Descriptive statistics will be used to summarize demographics and baseline information and to assess balance between the two groups (mean, standard deviation, minimum, maximum, and median for continuous variables; frequency and percent for categorical variables).

Analysis population

Statistical analysis for efficacy data will be carried out on an intention-to-treat (ITT) basis. An ITT set is defined as all patients who signed the informed consent form for the study enrollment and obtained an enrollment number. The treatment group of patients in the ITT set is the planned treatment group, i.e., according to the randomization list planned prior to the study commencement.

Statistical analysis for safety data will be carried out on an as-treated basis. An as-treated set is defined as all subjects who signed the informed consent form for the study enrollment and obtained an enrollment number. The treatment group of patients in the as-treated set is according to the treatment actually received.

Primary outcome

The primary outcomes include the mean of virological log reduction at Day 2, Day 3 and Day 4 and fever AUC above baseline. The virological log reduction of each patient will be measured at Day 2, Day 3 and Day 4 when they are inpatients. The mean of these three measurements will be computed for each patient, and then be compared between the two groups by a two-sample, one-sided t-test. The body temperature of each patient will be measured at baseline and from Day 1 to Day 5, and a curve of the temperature will be plotted. The area under this curve but above the baseline value will be computed for each patient, and then be compared between the two groups by a two-sample, one-sided t-test.

Secondary outcomes

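### Sections 3.2.3 and 6.2 give different rules for who enters the effectiveness analysis, and the ITT and as-treated sets are not tied to randomization or dosing

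*Protocol*

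**What the plan says.** Protocol section 3.2.3 (Premature Withdrawal of Patients from Study) sets two thresholds for patients who leave the study. For effectiveness: "All patients who withdraw early from the study but have received all days of study medication will be included in the analysis of effectiveness". For safety: "All patients who withdraw from the study but receive at least one dose of study medication will be included in the analysis of safety". The same section lets the investigator withdraw patients for adverse events and treatment failures, among other reasons, and says withdrawals are not replaced.

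Section 6.2 (Statistical analysis) states: "Statistical analysis for efficacy data will be carried out on an intention-to-treat (ITT) basis". It defines membership as follows: "An ITT set is defined as all patients who signed the informed consent form for the study enrollment and obtained an enrollment number". The planned group is taken from the randomization list. The safety set has the same entry condition: "An as-treated set is defined as all subjects who signed the informed consent form for the study enrollment and obtained an enrollment number". Its group is the treatment actually received.

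Section 5.6 stops study drug for severe dengue and for "any patient developing grade 3 severity diarrhoea". Section 5.1 says of patients who cannot finish the drug: "Patients unable to complete the entire course of drug treatment will be asked to complete all planned in-patient and out-patient assessments". In 5.1, enrollment and admission come first, then baseline assessment, then randomization.

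**The concern.** Placed next to the one-dose rule for safety, the effectiveness sentence in 3.2.3 has a purpose only if withdrawals with a partial course are left out. Under 6.2 the same patients are in. Two analysts who each followed one section would analyse different patients for both primary endpoints, the mean virological log reduction (VLR) over Days 2 to 4 and the fever AUC. No separate per-protocol set is named that would give the completer rule a supportive role.

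If the completer rule governed, patients withdrawn for an adverse event or treatment failure before the end of dosing would leave the primary comparison, and such reasons can depend on outcome or on treatment. Data already collected would also be discarded.

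A second, smaller weakness is that membership of both sets in 6.2 rests on consent and an enrollment number, not on being randomized or dosed.

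**Working it through.** **1. The two rules, patient by patient**

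| Patient | Effectiveness under 3.2.3 | Efficacy under 6.2 |
|---|---|---|
| Withdraws from study, full course taken | in | in |
| Withdraws from study, partial course | out (implied) | in |
| Stops drug, stays for assessments (5.1) | not addressed | in |

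The conflict is the second row. Table 2 shows what it can cost. The Day 2, 3 and 4 viremia samples are due at 23–24, 47–48 and 71–72 hours, while doses continue at 72, about 84 and 96 hours. A patient who withdraws between 72 and 96 hours can have all three VLR values and still not have received every day of drug.

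**2. The plan's own figures**

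Inputs from section 6.1: one-sided 5%, SD 1 log, 80% power, 1 log at 14 per group, 0.7 log at 25 per group. With the non-central t, power for 1 log is 79.7% at 13 per group and 82.4% at 14. For 0.7 log at 25 per group it is 78.7% (79.7% by the normal approximation). The stated figures reproduce and are not in dispute.

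**3. Illustration of bias under no true effect**

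Assumptions, not in the documents: k celgosivir patients and no placebo patients are excluded, and those k have a mean VLR 1 log below the rest of their arm.

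- Shift in the celgosivir mean: b = (k/25) × 1 log.
- Standard error with SD 1: √(1/25 + 1/(25−k)).
- Non-centrality: b / SE, with 48−k degrees of freedom.
- Type I error: the probability that this non-central t exceeds the one-sided 5% critical value.

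| k | b (log) | SE | Non-centrality | Type I error |
|---|---|---|---|---|
| 2 | 0.08 | 0.289 | 0.277 | 8.5% |
| 3 | 0.12 | 0.292 | 0.411 | 10.7% |
| 5 | 0.20 | 0.300 | 0.667 | 16.1% |

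The result depends heavily on the assumptions. With a 0.5 log deficit (b halved), the same formula gives 6.6%, 7.5% and 9.4%. With the exclusions on placebo only (b negative), it gives 2.8%, 2.0% and 1.1%, so the test becomes conservative. With equal numbers and equal deficits in both arms, b cancels and the error stays at about 5%.

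A simulation (40,000 runs, 25 per arm) dropped the k celgosivir patients with the worst exclusion score, where that score has an assumed correlation with VLR. For k = 3, type I error was 7.8%, 10.5% and 20.6% at correlations 0.3, 0.5 and 1. For k = 5 it was 9.5%, 14.1% and 34.3%. At zero correlation it stayed near 5%.

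No SD is given for fever AUC, so no matching figure can be worked out for that endpoint.

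**4. Power**

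Even without bias, exclusions cost power for 0.7 log: 76.2% at 22 versus 25 and 73.9% at 22 per arm, against 78.7% at full size.

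**5. Set membership**

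In 5.1 enrollment precedes randomization. A patient who has an enrollment number but is never randomized would meet the ITT definition with no planned group. One who is never dosed would meet the as-treated definition with no treatment received. The as-treated wording also differs from the one-dose rule that 3.2.3 applies to withdrawals.

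**The case against.** The statistical section plainly says ITT, and 3.2.3 says only that certain patients will be included, never that others are excluded. That is fair: the exclusion is implied. But the paired safety sentence makes the implication hard to avoid, and the document does not settle it.

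A reader might infer that everyone taken off drug for severe dengue or grade 3 diarrhoea drops out of the effectiveness analysis. The text does not support this. Section 5.6 stops study drug only, 5.1 asks those patients to complete all assessments, and the 3.2.3 sentence concerns withdrawal from the study. The exposed group is true withdrawals with partial dosing, mostly during a five-day inpatient stay, so it may be small.

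A reader might also infer that losses fall mainly on celgosivir. Diarrhoea is an expected drug effect, but 4.3 prescribes a diet to mitigate it, severe dengue can occur in either arm, and the safety hypothesis in section 2.2 expects no more events on celgosivir. Neither the direction nor the rate is given.

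The 6.2 sets are over-inclusive. They do not themselves exclude anyone because of outcome, and their group labels do use the randomization list and the treatment received. Section 5.2 says enrolled patients are randomized, and no text says when the enrollment number is issued, so an enrolled but unrandomized patient is possible, not shown. The inclusion criteria accept oral consent ("Able and willing to give written or oral informed consent") while 6.2 refers to signing. Concluding that orally consented patients fall out of ITT is over-literal, especially as the flowchart shows written consent.

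Finally, a patient who withdraws before Day 4 lacks some primary values under ITT too.

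**Conclusion.** The concern holds as a conflict between two stated rules for the primary population, with no statement of which governs. Since the protocol itself states both, this is not detail left to a later analysis plan. The completer reading can exclude study withdrawals for reasons tied to outcome or treatment. It does not reach patients who only stop drug and remain in follow-up.

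The size and direction of bias are unknown. The range of about 8.5% to 16% type I error rests on 2 to 5 exclusions, all on celgosivir, a 1 log deficit and SD 1 log. Only the SD comes from the protocol. It should not be read as an expected doubling or tripling of the error rate.

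The loose membership wording in 6.2 is a separate and lesser fault: it may admit patients who cannot be assigned to a group.

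**What to change.** - In 3.2.3, delete the effectiveness sentence or label it as defining a supportive per-protocol analysis.
- In 6.2, define the primary efficacy set as all randomized patients, analysed as randomized, using all collected viremia and temperature data whether or not the drug course was completed. Section 5.1 already asks for these assessments.
- In 6.2, define the safety set as all patients who received at least one dose, grouped by treatment received, and align 3.2.3 with it.
- Drop the signed form and the enrollment number as conditions for set membership.

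The cost is wording in two sections, with no new data or visits. It should be settled before unblinding. Values missing after true withdrawal will still need a stated method, so the change reduces the risk of bias without removing it.

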# Study Medication

## Drug Name, Formulation and Storage

Celgosivir is a butyl ester derivative of castanospermine, also known as 6-butanoyl castanospermine, castanospermine 6-butryate in the hydrochloride salt form or Bu-Cast. Its IUPAC name is [(1S,6S,7S,8R,8aR)-1,7,8-trihydroxy-1,2,3,5,6,7,8,8a-octahydroindolizin-6-yl] butanoate hydrochloride. The chemical formula is C12H21NO5HCl, molecular weight 295.75. The chemical structure is shown in Figure 1.

[figure not shown]

Figure 1: Chemical structure of celgosivir hydrochloride

Celgosivir is supplied as a capsule formulation containing 100 mg drug substance. No excipients are formulated with the drug. The drug is manufactured by Dalton Pharma Services, Inc., Toronto Canada at a GMP facility that holds a current Health Canada Establishment license.

Placebo is supplied as an identical capsule containing 100 mg pregelatinized maize starch. The placebo material conforms to the legal requirements of the US and European Pharmacopoeia.

Capsules should be stored at room temperature (15C ± 30C) at relative humidity <65%.

## Dosing Regimen

Patients will be given an initial loading dose of 400 mg (4capsules). Subsequent dosing will be 200 mg (2 capsule) every 12 hr. The patient will receive a total of nine (9) doses, one 400 mg dose and eight (8) 200 mg doses. The capsule(s) should be administered with ~15 mL water. Drug should be taken 1 hr before consuming food or 2 hr afterwards.

## Diet

To mitigate expected gastrointestinal effects (diarrhea and flatulence), patients will be placed on a special diet of protein, vitamins, and glucose containing minimal complex sugars or starches. Patients should be advised to avoid ingestion of sweets or starchy foods while on study drug.

## Concomitant Medications

Patients may continue their baseline medication(s). Patients may be administered paracetamol according to the Principal Investigator’s or Co-investigators’ instructions. The daily dose of all medications should be recorded on the appropriate pages of the CRF.

## Drug Accountability

Upon receipt of drug product, the pharmacist affiliated with the IMU will be responsible for taking an inventory of the investigational drug and placebo agents. A record of this inventory must be kept and usage must be documented on drug inventory forms. The record must be available for inspection by the medical monitor, IRB or regulatory authorities.

# Study Procedures

## Methods and Assessments

Patients who present at the polyclinics, Tan Tock Seng Hospital, at the Emergency Departments (ED), SGH and NUH, at general practitioner’s office, or are self-referred, male or female, age 21 to 60, who have fever  38C of  48 hr duration, at least two criteria indicating probable dengue infection, and a positive NS1 strip assay will be referred to the Investigational Medicine Unit (IMU) to undergo screening. Eligible patients will be approached and invited for participation. The patient will be given the patient information sheet and allowed to ask any questions about the trial. The Principal Investigator or a Co-investigator will take informed consent. Patients meeting all inclusion and exclusion criteria and who agree to participate will be enrolled and admitted to the Investigational Medicine Unit (IMU).

A flowchart showing the patients’ activities throughout the whole study is shown in . A table summarizing the assessment schedule for the study is shown in the Appendix, Table 2.

Upon admission, a clinical examination will be conducted, including ECG and chest X-ray. Blood samples will be taken for baseline assessments - viremia, quantitative NS1, IgG specific for previous dengue infection, hematology and coagulation, clinical chemistry, immunological profile, pre-dose pharmacokinetics, and DNA and RNA analysis. Urine will be collected for a pregnancy test (female patients only) and urine protein/ creatinine ratio and urinalysis (all patients). The patient will be asked to complete a visual analog scale for pain (VASP). The patient will then be randomized to placebo or celgosivir group. Capsules will be administered without food from Day 1 to Day 5. Patients will be placed on a special diet of protein, vitamins, and glucose containing minimal complex sugars or starches. Oral fluid intake, urine output, and stool frequency and consistency will be recorded, as well as any adverse events. Daily clinical exams will be conducted. Blood samples will be drawn daily while in hospital for hematology and clinical chemistry, viremia, quantitative NS1 levels, and immunological profiling (RNA expression levels and cytokines). Any subject who has a platelet count drop of ≥50,000/mm3 over a 24 hour period will require full blood count monitoring every 12 hr henceforth until platelet count trend reverses. Urinalysis will be conducted daily, and a sample of urine will be reserved for PK drug levels. Patients also will be asked to complete a VASP daily. Pain medications and any other concomitant medications will be recorded (date/time of ingestion and amount). Over the course of the hospital stay, eight blood samples will be obtained for pharmacokinetic assessments: one pre-dose sample will be taken on Study Day 1, three samples will be obtained on Study Days 2 through 4 between 1 to 3 hr after ingestion of drug (peak levels), and four samples will be obtained on Study Days 2 through 5 immediately prior to ingestion of the next dose (trough levels). The date and time of pharmacokinetic blood draws will be recorded on the CRF. On Study Day 5, after blood draws, administration of the last dose, safety assessments, determination of risk for DHF or DSS, and satisfactory clinical status, the patient will be discharged. Patients at risk for or who have dengue hemorrhagic fever (DHF) or dengue shock syndrome (DSS) will be transferred to a medical ward of the hospital until fit for discharge. Patients who progress to DHF or DSS may require intravenous fluids, platelet and/or blood transfusions and evaluations from other clinical specialists. They will be treated according to standard of care for DHF and DSS--primarily bed rest, fluids, as well as fever and pain medications (supportive therapy).

Patients will be asked to return to the IMU on Study Days 7, 10, and 15 for blood draws, urinalysis, completion of a VASP, and safety assessments. Estimated total blood volume taken per patient is ~ 200 mL during Study Days 1 to 5 and ~ 80 mL for Study Days 7 to 15. The patient will complete the study on Study Day 15 after the investigator has completed the final assessment, unless ongoing adverse events require monitoring. Patients unable to complete the entire course of drug treatment will be asked to complete all planned in-patient and out-patient assessments.

The sponsor will cover all costs for drugs, procedures, consumables and hospitalization stay (Class A ward) related to dengue illness through Day 15 or effects related to celgosivir usage. Participants in the trial will receive compensation for participation in the study.

## Randomization

Enrolled patients will be randomized into one of the two groups in the same ratio (1:1). Randomly permuted blocks will be used to ensure balance over time. The block length will be determined by the randomization statistician and will not be made known to the clinical investigators and site personnel. Randomization will be carried out via a web-based randomization system hosted by the Singapore Clinical Research Institute (SCRI). Only authorized personnel will be allowed to access the system via a password-protected web site available 24 hours a day. Back-up randomization opaque envelopes (and related procedures) will also be prepared and provided to the site in case of any internet failure.

